## Abstract

**Introduction:**

Youth placed in out-of-home care is a large and highly vulnerable group at high risk of negative developmental outcomes. Given the size and extent of negative developmental outcomes for youth placed in out-of-home care, interventions to help this vulnerable group navigate successfully towards independent living and promote wellbeing across a spectrum of outcome areas are needed. To date, there is a lack of such interventions, particularly in Sweden. Importing interventions from other societies and cultures is associated with difficulties. The aim of the research project is to implement, test, and evaluate interventions that have been recently developed in Swedish practice to close this gap.

**Methods:**

The project has an ambitious and complex data collection and analysis strategy using qualitative, quantitative, and multiple information methods (hybrid effectiveness-implementation study) over the course of two years. Both the implementation and effectiveness of the interventions will be evaluated. The recently developed My Choice-My Way! leaving care program for youth aged 15+ will be the primary focus of the project and will be compared to usual services.

**Conclusions:**

The project has the potential to offer novel insights into how society can promote wellbeing across a spectrum of outcome areas for the high-risk group of youth transitioning from out-of-home care to independent living. As such, the project will have important implications for both research and practice.

**Trial registration:**

ClinicalTrials.gov Identifier: NCT05813197.

## Introduction

### Background and rationale

This protocol describes an applied Swedish research project on how to promote the well-being across a spectrum of outcome areas for youth transitioning from out-of-home care to independent living.

Youth placed in out-of-home care is a large and highly vulnerable group with high risks of negative, developmental outcomes. About 3–4% of Swedish children are placed in out-of-home care (i.e., care situations where youth live outside of their own home e.g., foster care, group home care, institutional care) at some point and about 1% of children grow-up primarily in out-of-home care [1]. Most of the children placed in out-of-home care are teenagers. Swedish research continually shows that these youth transition to independent living and adulthood with relative disadvantage in all types of health related outcomes (e.g. somatic, mental, and dental; see meticulous review by [2]), educational attainment [3], housing stability [4], early childbearing and reproductive health [5], substance abuse [6], offending [7], exclusion from or weak attachment to the labor market [8], and public welfare dependency [7] compared to their non-placed peers. This negative development pattern is consistent across studies regardless of outcome, choice of comparison group, methodological approach, or location of study.

Given the size and extent of negative developmental outcomes for youth placed in out-of-home care, interventions to help this vulnerable group navigate successfully towards independent living and promote wellbeing across a spectrum of outcome areas are needed. Unlike other countries there is no legislation regarding the provision of transition services for this group in Sweden. Current practice places emphasis on activities which occur prior to placement (e.g., recruitment of foster families) with little to no interventions provided for support of children during ongoing care [9]. None of the strategies for care of children in out-of-home care currently in use in Sweden have been evaluated for their effectiveness (ibid). There is very little research regarding the effectiveness of interventions for transition aged youth. A review [10] concluded that youth aging out of out-of-home care who participate in the programs investigated obtain some productive outcomes but that comparisons with nonparticipant youth and comparisons between interventions could not be made because the studies included in the review were poorly designed. Another review of interventions designed to improve the physical and mental health of children placed in foster care [9], found that outcomes in this group can be improved but only three of 18 specific interventions had more than “some reliable evidence of effectiveness” (p. 7). Only one of these targeted youth themselves. This result was mirrored in a review of transition services for youth leaving out-of-home care which found that Independent Living Services which adapt services to youth needs can have positive results [11].

Across systematic reviews [9, 11, 12] the potential of self-determination interventions to improve outcomes for this population has been highlighted. Self-determination originates from multiple youth-oriented fields [13] where consensus has emerged around self-determination as a developmental protective factor [14]. A growing body of research has affirmed the promotive role of self-determination in positive youth development [13], and in quality-of-life outcomes (including internalizing and externalizing behaviors) for youth [15]. Intervention to enhance self-determination focuses on the intention to make decisions, to direct one’s actions, and to exercise rights and responsibilities, within the context of an individual’s culture, experiences, and aspirations. Experimental tests of interventions based on self-determination theory are few, have small sample sizes, and have not been replicated. Two intervention components have been replicated across self-determination enhancement studies: youth-directed skill-building to develop specific competencies for accomplishing transition-related goals (selecting goals, problem-solving, self-regulation; [16]), and consistency in promoting positive youth attitudes and beliefs around their capacity for self-determination in their lives [17]. Specific tests of mechanism-based mediation are lacking. This means that even though interventions of this type appear to be promising and have some empirical support for their effectiveness, the causal link between specific program components (e.g., goal setting), theoretical constructs (e.g., behavior regulation) and outcome (e.g., educational achievement) has yet to be tested. Increasing our understanding of *how* specific activities impact change processes has the potential of aiding our ability to design effective programs in the future.

#### Linking behavior change techniques (professional practice components) with mechanisms of action (theoretical constructs) and outcome (client level behavior change)

Little is known about how we might put into practice specific activities (i.e., program content) to impact specific change mechanisms (i.e., constructs) in order to impact outcomes for individuals, groups and society. There exists an abundance of behavior change techniques (e.g., goal setting, problem solving; [18, 19] available as well as theoretical models of behavior and behavior change (e.g., self-determination theory, social cognitive theory; [20]) but empirical testing of the links between these two is lacking [19]. Increased understanding of these links is key to informing the development of effective interventions by providing information on the strategies and target mechanisms likely to be effective in specific contexts and among specific populations [21]. A similar shortcoming concerns the link between change mechanisms and outcome. Recent meta-reviews of interventions across a range of contexts and populations have brought to light the limited extent to which primary studies include theory-based measures of the dependent variable, tend not to conduct the appropriate analyses to test intervention change mechanisms, do not provide enough information for secondary analyses of change mechanisms, and do not specify a proposed theory-based mechanism for the effect of the intervention on individual behavior [22–24]. Although primary studies of the effectiveness of interventions test the effects of intervention on outcome, assessment of how a successful intervention changes behavior is lacking (i.e., via a priori planned and appropriately powered mediation analysis; [23]).

#### Implementing promising interventions within human service organizations

In order for effective interventions to produce positive change in individuals, the implementation process within human service organizations (e.g., municipal social services, NGOs) must also be effective. Few programs survive after the initial implementation period to become a sustained, integral part of regular service (for review, see [25]). Organizations could cease the use of the new program entirely or they could significantly alter it in a way that may or may not be desirable given the current context and target group (for a Swedish example see, [26]). The understanding that interventions can fail due to theoretical deficiencies in the intervention itself or shortcomings in the implementation process has led to increased focus on *how* we might systematically carry out implementation efforts in order to improve implementation effectiveness when moving interventions into practice (for a review of implementation theories, models and frameworks see [27]).

Getting to Outcomes (GTO, [28]) is both an implementation model for carrying out intervention activities, and a support intervention aimed at enhancing practitioner capacity. Built on social cognitive theories of behavioral change and implementation science theories such as the Consolidated Framework for Implementation Research [29], developers purport that GTO builds practitioner capacity to perform multiple implementation best practices needed for interventions. Improved performance of these implementation best practices when delivering a specific intervention may improve intervention fidelity, which should result in more positive outcomes for clients. GTO has been applied to several content areas with active involvement of GTO model developers. Although GTO is an open source material this leaves questions as to whether GTO can effectively be used as a general implementation support (i.e., without developer support or involvement) to boost program effectiveness and sustainability.

#### Project novelty

This project is novel in a number of ways. First, this project weaves together several complementary areas of research to meet the needs of the municipal social services and the youth in its care (i.e., implementation science, intervention science, developmental psychology, social work). Second, this research will experimentally test the effects of a locally developed, theoretically and empirically inspired intervention developed based on cutting-edge intervention development theory in collaboration with municipal stakeholders aiming to support an underserved and extremely vulnerable group, one of the municipal social services core populations. Third, this project will experimentally test the extent to which implementation support impacts fidelity, sustainability and client outcomes. Fourth, this research will increase our empirical understanding of how specific behavior change techniques (practice components) are related to theoretical change mechanisms (constructs) and how these constructs in turn are related to youth outcomes. This has the prospect of increasing our scientific knowledge of how intervention development and implementation can be approached in the future. Finally, there are currently no evidence-based and culturally sensitive interventions available to social service professionals for this population and purpose. Our work has the goal of developing our knowledge toward meeting this challenge.

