### Objectives

The purpose of this project is to increase our understanding of how to promote the well-being across a spectrum of outcome areas for youth (15 + years old) transitioning from out-of-home care to independent living through the study of the implementation and provision of (A) My Choice—My Way! (*Swe*. Mitt val–min väg!) and (B) Usual Services. This includes an increased understanding of how interventions for this population can be designed, implemented, and sustained in diverse settings.

The project has five specific aims and eleven research questions.

#### Aim 1

To test the short- and sustained effectiveness of My Choice-My Way! in normal practice settings.

H1: Youth participating in My Choice-My Way! will exhibit gains in well-being and psychosocial outcomes relative to youth participating in Usual Services.

*Research questions*. RQ1 What is the relative effectiveness of My Choice-My Way! and Usual Services (US) for youth aged 15 and older in out-of-home care on well-being and psychosocial outcomes?

RQ2 How are outcomes moderated by subgroup characteristics?

RQ3 How does implementation fidelity moderate outcomes?

RQ4 What is the relative economic impact of My Choice–My Way!?

#### Aim 2

To advance our understanding of how specific behavior change techniques and theory-based change mechanisms impact youth outcomes.

H2: Theoretically based change mechanisms (e.g., experiences of success targeting self-efficacy change) will have a mediating effect on outcome (e.g., increased engagement in educational activities) in interventions with detailed program content.

*Research questions*. RQ5 How are the specific behavior change techniques used by social workers related to theoretical change mechanisms?

RQ6 How do the specific change mechanisms in transition services mediate youth outcomes?

#### Aim 3

To assess the extent to which implementation support (i.e., GTO) can impact fidelity and sustainability in practice settings.

H3: Organizations engaging in implementation support will exhibit increased fidelity relative organizations not engaging in implementation support.H4: Organizations engaging in implementation support will exhibit increased sustainability relative organizations not engaging in implementation support.

*Research questions*. RQ7 How does implementation support impact fidelity?

RQ8 How does implementation support impact sustainability?

#### Aim 4

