### Trial design

The study can be described as a hybrid effectiveness-implementation study with natural controls in a quasi-experimental two-arm study design [30]. We will conduct such a study to test the impact of the leaving care interventions while we at the same time collect data on the implementation process and outcomes (i.e., Hybrid I design). Research design and methods for data analysis specifically linked to each of the aims and research questions will be described in more detail below.

#### Design Aim 1

We will perform an effectiveness study to achieve Aim 1 and to answer RQ1-RQ4. The effectiveness study will be carried out as a natural quasi-experiment with two groups of youth participants (My Choice–My Way!, US) with dependent pre-, post- and follow-up measures [31] (i.e., 3 x 3 mixed factorial design. Long-term outcomes will be studied with a longitudinal register study.

#### Design Aim 2

Based on the My Choice–My Way! theory of change (i.e., logic model, [32]) salient change mechanisms will be chosen and measured.

#### Design Aim 3

Posttest comparison study comparing implementation and youth level outcomes for organizations engaged in implementation support with organizations not receiving implementation support.

#### Design Aim 4

Qualitative implementation, posttest interview study with service providers.

#### Design Aim 5

Qualitative implementation, posttest interview study with youth participants.

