### Study setting

This is a multicenter research project that will be conducted at a total of 21 research sites throughout Sweden. Organizations have naturally self-selected to either implement My Choice–My way! (*n* = 12) or to continue providing Usual Services (US, *n* = 9). All twelve organizations that implement My Choice—My Way! are part of the Swedish social services, although some are public and others private providers of services to youth. The nine organizations that constitute the control group and provide US are various organizations that provide support for the target group either within the Swedish social services or as a part of civil society. A list of study sites can be obtained from the first author of this protocol.

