### Allocation

This study will follow the natural assignment of youth to condition (i.e., the research team will not manipulate the normal operating procedures of the participating municipalities/organizations but instead will follow youth as they are assigned to My Choice–My Way! and US). We will implement a rolling inclusion. Youth will be admitted to the study as they are referred to one of the study arms (My Choice–My Way!, US). Inclusion to the study will continue until we have included the desired number of participants.

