#### Aim 3 statistical methods

*RQ7*. Fidelity ratings from the systematic session observation at T2 will be compared across My Choice–My Way! groups to investigate differences in implementation quality (e.g., independent samples t-test, Mann-Whitney U depending on final data characteristics).

*RQ8*. Fidelity measures collected from My Choice–My Way! T3 will be compared (e.g., ANOVA) for significant differences between groups.

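### The protocol claims an experimental test of implementation support, but the design it describes for Aim 3 is an unassigned posttest comparison that supports only an association among at most 12 organisations

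*Protocol article*

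**What the plan says.** The Project novelty section lists, among the study's new features, that "this project will experimentally test the extent to which implementation support impacts fidelity, sustainability and client outcomes". It uses the same adverb for the test of My Choice–My Way! itself.

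The Trial design section describes a "hybrid effectiveness-implementation study with natural controls in a quasi-experimental two-arm study design". For Aim 3 it specifies a "Posttest comparison study comparing implementation and youth level outcomes for organizations engaged in implementation support with organizations not receiving implementation support". H3, under Objectives, reads "Organizations engaging in implementation support will exhibit increased fidelity relative organizations not engaging in implementation support", and H4 has the same form for sustainability. Aim 3, RQ7 and RQ8 speak of the impact of support.

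Under Study setting, "Organizations have naturally self-selected to either implement" the programme (12 organisations) or continue with Usual Services (9). The same section says that some of the twelve are public providers and others private.

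Under Aim 3 statistical methods, RQ7 compares fidelity ratings between My Choice–My Way! groups ("e.g., independent samples t-test, Mann-Whitney U depending on final data characteristics"). RQ8 compares fidelity at T3, with ANOVA as the example. The instruction to control statistically for identified baseline differences appears under Aim 1 statistical methods and concerns background and outcome variables at T1.

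**The concern.** An experiment requires that someone assigns the exposure. The article describes no assignment of implementation support, and its Trial design section uses the vocabulary of a non-randomised comparison. The claim under Project novelty and the design under Trial design cannot both stand.

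This matters because the article is the public, prospective statement of what the study can establish. A later report could cite it to present a difference in fidelity as the effect of support. With a posttest-only comparison of unassigned groups, the same difference could come from whatever else separates the two sets of organisations. The article itself names one candidate, public versus private provision. The methods named for RQ7 offer no way to account for it.

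**Working it through.** The plan gives no sample size, power or effect size for Aim 3, so there is no figure to reproduce. The check is of the text, followed by the algebra of the bias and an illustration under stated assumptions.

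**Step 1: claim against design**

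| Element | Where | Content |
|---|---|---|
| Claim | Project novelty | experimental test of programme and of support |
| Overall design | Trial design | "natural controls in a quasi-experimental two-arm study design" |
| Aim 3 design | Trial design | posttest comparison of organisations with and without support |
| Assignment of support | anywhere | not described |
| Entry to the programme | Study setting | self-selection by organisations |
| Tests for RQ7 | Aim 3 statistical methods | t-test or Mann-Whitney U, as examples |
| Rule for adjustment | Aim 1 statistical methods | T1 background and outcome variables |

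For RQ2 and RQ3 the article names regression-based moderation and ANCOVA. For RQ7 both named tests are unadjusted, and the choice between them depends on the data's characteristics, not on confounding.

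**Step 2: what the unadjusted difference estimates**

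Let τ be the effect of support, and δ the mean difference in fidelity that supported and unsupported organisations would show if neither had support. Then

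E(difference in means) = τ + δ.

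Random assignment makes δ zero in expectation. Without assignment, without a pre-support fidelity value and without covariates, τ and δ cannot be separated. The bias is δ in full, and recruiting more youth does not reduce it.

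**Step 3: illustration**

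The group splits, the shifts and the intraclass correlation (ICC) are assumptions; the article gives none of them. The true effect τ is set to 0 and the test is two-sided at 5%.

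*Organisation means as the unit.* With a supported and b unsupported organisations, df = a + b − 2 = 10 and the noncentrality is δ·√(ab/(a+b)), with δ in SDs of organisation means.

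- 6 v 6: √(36/12) = 1.732. For δ = 0.5, 0.8, 1.0 the noncentrality is 0.87, 1.39, 1.73.
- 4 v 8: √(32/12) = 1.633. The corresponding values are 0.82, 1.31, 1.63.

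| δ (SD) | Rejection, 6 v 6 | Rejection, 4 v 8 |
|---|---|---|
| 0 | 0.05 | 0.05 |
| 0.5 | 0.12 | 0.12 |
| 0.8 | 0.24 | 0.22 |
| 1.0 | 0.35 | 0.32 |

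*Single recordings as the unit.* Two sessions for each of 80 youth give 160 recordings, and 160/12 ≈ 13 per organisation. In a simulation of 4,000 runs with 6 v 6 organisations and δ in SDs of single recordings, the t-test treating recordings as independent gave:

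| δ (SD) | ICC 0 | ICC 0.10 |
|---|---|---|
| 0 | 0.05 | 0.19 |
| 0.5 | 0.87 | 0.79 |

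At an ICC of 0.10 the test rejects in 19% of runs even with no pre-existing difference, because recordings from one organisation are not independent. The fix therefore has to deal with the unit of analysis as well as with confounding.

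**The case against.** **The article does not say how support was allocated.** This stands. A reader might infer that organisations choose support for themselves, but no section says so. The self-selection under Study setting is between My Choice–My Way! and Usual Services. The statement under Allocation that "the research team will not manipulate the normal operating procedures of the participating municipalities/organizations" concerns the assignment of youth to the two arms and does not mention support. The Aim 3 wording would also fit support that the team had assigned. A condensed article may leave that detail to the full protocol, so silence on it is not itself the fault. The fault is a claim of an experiment beside a description that is not one.

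**The RQ7 tests are examples.** This also stands. Adjustment is not excluded, and it would be wrong to say that the plan commits to an unadjusted analysis. Still, the only tests named cannot take a covariate, and the only adjustment rule belongs to another aim.

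**H3 is worded as a contrast.** Correct: H3 and H4 do not themselves credit support with the difference. The causal reading comes from Project novelty and from the word impact in Aim 3, RQ7 and RQ8.

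**A pre-support fidelity value is not obtainable.** Largely true, since fidelity is scored from sessions of the programme. This is a limit of the design, not an oversight, and it is a further reason not to call the comparison experimental.

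**No false-positive rate can be quoted.** A reader might want one figure for the damage. The documents do not support one: at a shift of 0.5 SD the illustration runs from 0.12 to 0.87, depending on the unit and on which SD is meant.

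**Conclusion.** The point holds as a mismatch between claim and design. The article announces an experimental test of the programme and of implementation support, while its Trial design section describes natural controls and, for Aim 3, a posttest comparison with no described assignment. As written, Aim 3 supports an association among at most 12 organisations.

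The RQ7 estimate is biased by the whole of any pre-existing difference in fidelity, but the size of that difference cannot be given, because neither the split by support nor the variance of fidelity is stated. The rejection rates above show only how the problem behaves under assumed values. That organisations selected themselves into support, and that RQ7 will be analysed without adjustment, are inferences that the text permits but does not state.

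Aim 3 is separate from the primary youth outcomes. For the programme comparison only the wording is at issue here, since Aim 1 has its own adjustment rule.

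**What to change.** 1. Under Project novelty, replace the claim of an experimental test, for the programme and for support, with wording such as: compare in a quasi-experimental design.
2. For RQ7 and RQ8, replace the unadjusted comparisons with an analysis that has organisation as the unit or as a cluster effect, adjusted for public or private provider status. Keep the covariates to that one. Provider role should not be added: organisations choose their providers, so role may lie on the path from support to fidelity, and the article does not say that it is recorded for analysis.
3. Report RQ7 and RQ8 (H3 and H4) as adjusted associations, not as the impact of support.
4. If the team did assign support, say how and analyse by assignment. The experimental wording for support could then be kept, to the extent that the assignment justifies it.

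The cost is mainly wording, plus a model using a characteristic of each organisation that the article already describes. With organisation as the unit, the covariate reduces the residual degrees of freedom from 12 − 2 = 10 to 12 − 3 = 9. Confounding by unmeasured features of the organisations remains, and the claim becomes weaker, so the change of wording is needed even with the adjusted model.
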